## Abstract

**Background:**

Many patients during manual therapy after anterior ligament reconstruction will experience severe pain, which has a negative impact on their rehabilitation. However, there is rarely an analgesic method for these patients during rehabilitation. Nitrous oxide with rapid analgesic and sedative effects is often used to relieve pain in minor procedures. The purpose of this study is to determine whether or not nitrous oxide analgesia decreases pain compared to oxygen during manual therapy after anterior ligament reconstruction.

**Methods/design:**

This single-center, randomized, double-blind and controlled trial will recruit 120 patients. Patients ≥ 18 years old undergoing manual therapy after anterior ligament reconstruction (1 month post-operative) with acute pain (VAS ≥ 4) are included. The main exclusion criteria included the following: pulmonary embolism, intestinal obstruction, pneumothorax. Patients will be randomly allocated to the intervention group (A) and the control group (B) in a ratio of 1:1. Doctors, therapists, patients, and data collectors are all blind to the study. The manual therapy will be performed by therapists. Nurses who implemented the intervention handed the doctors envelopes containing the patients’ codes and allocation of A or B. Group A will receive a pre-prepared nitrous oxide/oxygen mixture plus conventional treatment (no analgesic) given as 30-min treatment sessions, once daily, and group B will receive oxygen plus conventional treatment (no analgesic) under the same conditions. Assessments will be taken 2 min before the intervention (T0), 5 min after the beginning of the intervention (T1), and 5 min after the intervention finished (T2). The primary outcome is pain score. Secondary outcomes include vital signs, side effects, joint range of motion, adjuvant analgesia need, therapist and patient satisfaction, and whether willing to receive the same gas again.

**Expected outcomes:**

We expect nitrous oxide inhalation to have a beneficial effect on the pain of patients who receive manual therapy after anterior ligament reconstruction.

**Discussion:**

If this treatment appears beneficial, it could improve patients’ satisfaction and quality of life potentially and even be implemented widely in hospital and rehabilitation settings.

**Trial registration:**

ClinicalTrials.gov identifier, ChiCTR2200061175 (Version 2.0 June 15, 2022), https://www.chictr.org.cn.

**Supplementary Information:**

The online version contains supplementary material available at 10.1186/s13063-023-07732-z.

## Introduction

Anterior cruciate ligament (ACL) reconstruction is one of the most common operations in orthopedic [1]. ACL reconstruction after a ligament tear has been considered the key to treatment, especially for those wishing to resume normal life [2]. However, considerable postoperative complications such as pain, swelling, and a sudden impairment of motor function, muscle contracture, and joint stiffness may occur after ACL reconstruction surgery [1, 3]. Rapid return to normal function after surgery is a desirable result for patients and health providers. Rehabilitation is imperative to implement for alleviating pain and joint range of motion (ROM) gain [4]. Manual therapy (MT) after ligament reconstruction includes passive joint movement, joint stretching, free hand strength training, and other techniques, which are widely used in the postoperative recovery of various musculoskeletal diseases [5]. The effect of the technique can be attributed to the mechanisms of improving soft tissue ductility, stimulating peripheral mechanical receptors, and triggering neurophysiological responses [6, 7]. Rehabilitation after ACL reconstruction is painful as it generally begins early post-surgery. The experience of anxiety and fear also increases the perception of pain and even hinders the patients’ compliance with future treatment, which ultimately impacts surgical results [8]. Pain management during rehabilitation may reduce the incidence of complications, improve quality of life, shorten hospital stays, and reduce health care costs [9].

Oral or intravenous analgesics are usually used for immediate to short-term postoperative pain, but there is no systematic rehabilitation period analgesia program through literature review. Commonly used drugs include systemic opioids, non-steroidal anti-inflammatory drugs, and gabapentinoids [10, 11]. Although they can alleviate pain, it has many side effects concurrently, such as nausea and vomiting, lethargy and over-sedation, respiratory depression, and gastrointestinal tract damage [12]. These side effects may lead to delayed recovery after anesthesia or early postoperative recovery, increasing the length of stay and reducing patient satisfaction. Nitrous oxide (N_2_O), as an analgesic and sedative, which has the advantages of simple handling, fast onset, good effect, and few adverse reactions, is commonly used in various painful procedures [13]. Different studies have reported that the use of N_2_O can bring about notable pain relief in different areas of medicine such as minor dental surgery, emergency trauma, labor analgesia, plastic operation, colonoscopy, cancer pain, bone marrow biopsy, and invasive operation in pediatrics [14–21]. It usually produces effective and transient analgesia without changing consciousness and cognition, so patients can soberly cooperate with therapists during treatment. The device is portable and cheap, and patients can control it easily. It was observed that all side effects (dizziness, euphoria, nausea, vomiting, etc.) were temporary and disappeared within 5 min after stopping inhalation. No serious complications were found [22, 23].

There is an absence of a trial assessing the efficacy of N_2_O with MT after ACL reconstruction surgery. It is required that reasonable analgesia for patients who underwent MT. Thus, the purpose of this study is to evaluate the analgesic effect of inhaling N_2_O during rehabilitation on patients receiving MT through a randomized double-blind controlled trial. We hypothesized that its analgesic properties would decrease pain compared to placebo during MT with few side effects.

## Method

### Study design

The proposed clinical trial will be a single-center, randomized, double-blind, and controlled intervention study for the analgesic effect and safety of N_2_O during MT. It is registered in the Chinese Clinical Trial Registry (ChiCTR2200061175) and is in full adherence to the principles of the Declaration of Helsinki and Good Clinical Practice (GCP) guidelines. This trial will be conducted at the rehabilitation department of the 960th Hospital of PLA in China, and 120 patients will be randomly enrolled in two regimen arms with a ratio of 1:1; the recruitment will begin in July 2022. Although this study is a single-center, further multi-center clinical trials will be conducted in the future to provide more reliable evidence for the research results. The data collection phases of the CONSORT flow chart and the schedule of enrolment, and interventions are shown in Fig. 1 and Table 1, respectively.

**Fig. 1 Fig1:**
[figure not shown]
The CONSORT flow chart

**Table 1 Tab1:** Schedule of inclusion, interventions and assessments

**Time points**	**Study period**					
	**Enrolment**		**Post-allocation**			**Close-out**
	Patients with acute pain caused by manual treatment after anterior ligament reconstruction		T0	T1	T2	Data collection measurements
**Patients**						
Eligibility screen	√					
Informed consent	√					
Allocation	√		√			
**Interventions**						
Intervention group				√		
Control group				√		
**Assessments**						
Pain score			√	√	√	Visual analogue scale
BP			√	√	√	Non-invasive electronic manometer
HR			√	√	√	Digital monitoring
SPO_2_			√	√	√	Digital monitoring
Side effects				√	√	Yes/no
ROM					√	Goniometer
Satisfaction					√	Satisfied/dissatisfied
Adjuvant analgesia					√	Yes/no
Acceptance					√	Yes/no

*Abbreviations*: *BP* blood pressure(mm/Hg), *HR* heart rate(bpm), *SPO*_*2*_ oxygen saturation(%), *ROM* range of motion(°)

### Ethics and dissemination

This protocol has been approved by the Ethics Committee (2021–59). We will protect the rights and safety of participants by full compliance with the Declaration of Helsinki and GCP guidelines. We will obtain written informed consent from the participants. Appropriate measures will be taken to ensure the confidentiality of data gathered in this study. The results of this study will be disseminated to the public through relevant academic and professional journals and conferences.

Any amendment to the protocol which may influence the conduct of the trial, the potential benefit or safety of the patient, including changes in study objectives, study design, patient population, sample sizes, or study procedures will require a formal modification to the protocol. Such modifications will be agreed upon by all members of the trial, and approved by the Ethics Committee before implementation and notified to the trial registries, journals, and regulators.

### Participants

All patients who received MT after ACL reconstruction facing acute pain will be invited to participate in this study. To decrease confounding factors that may interfere with pain scores during the rehabilitation, we will recruit patients with relatively consistent surgical site as much as possible (unilateral joint). The inclusion criteria are as follows: willing to participate in the trial and sign informed consent; man or woman; age ≥ 18 years old; patients underwent primary unilateral ACL reconstruction (1 month post-operative, with or without meniscal injury or collateral injury); experience worst pain (during MT) was reported ≥ 4 (on a visual analogue scale (VAS) of 0–10 cm); without postoperative complication. Exclusion criteria include the following: patients with pain unrelated to MT; patients who have undergone other surgical operations on the knee except for ACL; mental disorder or altered mental status have difficulty in reporting pain; patients with contraindications to N_2_O (abdominal distension or suspected bowel obstruction, air embolism, pneumothorax, decompression sickness, epilepsy, pulmonary cancer, chronic obstructive pulmonary disease and acute respiratory infection, pregnancy, severe inhalation injury, pharmaceutical or pathological pulmonary fibrosis, maxillofacial injuries, disease involving ear, nose, larynx, such as sinuses, otitis media); drug dependence or abuse. The main inclusion and exclusion criteria are presented in Table 2.

**Table 2 Tab2:** Main inclusion and exclusion criteria

**Inclusion criteria**	**Exclusion criteria**
Patients with acute pain caused by manual treatment after anterior ligament reconstruction	Patients with mental disorder or altered mental status have difficulty in reporting pain
Age ≥ 18 years old	Patients who have undergone other surgical operations on the knee except for ACL
Willing to participate in the trial and sign informed consent	Drug dependence or abuse
Background worst pain (during Manual therapy) reported being 4 or higher (on a visual analogue scale (VAS) of 0 to 10 cm)	Contraindications to N_2_O (suspected bowel obstruction, air embolism, pneumothorax, epilepsy, chronic obstructive pulmonary disease, and acute respiratory infection, pregnancy, pharmaceutical or pathological pulmonary fibrosis, maxillofacial injuries, disease involving ear, nose, larynx)
Without postoperative complication	

### Recruitment strategies

Potential participants for the study will be sourced from the 960th Hospital of PLA, which is a general hospital in Shandong. Recruitment sources will be focused on patients who undergoing MT after ACL reconstruction. A researcher of the team will contact the case managers, participants, and other relevant staff for information about the study. Researchers will introduce the details to patients so that they can fully understand the potential benefits and risks of participating in this study. If that patient is interested in participating, they will voluntarily contact the researcher and complete a “consent to contact form.” Special researchers assess that the participants who meet the inclusion criteria will sign the “informed consent form.” The two gases will be provided to the participants free of charge. Participants will be provided with professional medical services and disease assessment by medical workers throughout the study period to encourage patients to complete the entire study. Appropriate compensation will be given to the participants for the inconvenience of time or any harm by the trial.

### Randomization, allocation, concealment and blinding

To minimize selective bias, a member of our research team is not involved in any other section of the study. Eligible patients will be randomly divided into the intervention and control groups with a ratio of 1:1 to receive: 30-min inhalation of pre-prepared nitrous oxide/oxygen mixture plus conventional treatment (no analgesic) or inhalation of placebo consisting of oxygen plus conventional treatment (no analgesic) for 30 min. Before initiating recruitment, the randomization sequence is generated and validated by a statistician using Microsoft Excel and then kept by an administrator who does not participate in this study. The list will be sealed in an envelope and stored in a designated room to ensure concealment. After participants meet all the inclusion criteria and complete the baseline assessment, the project manager will apply for random numbers and the patients will receive the corresponding treatment. Except for the project manager, who is responsible for gas distribution, other researchers, operators, and patients do not know the allocation, to ensure the implementation of blinding. In addition, considering that two gases will significantly affect the outcome of this trial, all cylinders with the same appearance containing N_2_O and O_2_ will be covered with labels A and B until completing all the procedures of this trial.

To maintain the overall quality and legitimacy of the study, code breaks should occur only in exceptional circumstances such as serious side effects when knowledge of the actual treatment is essential for further management of the patient. If unblinding is deemed to be necessary, the researcher should use the emergency system for unblinding.

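### Two shared cylinder letters that match the published arm names, and conflicting accounts of who sees the A/B allocation, do not secure the stated double blind

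*Protocol article*

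**What the plan says.** The abstract of the protocol article (Methods/design) names the arms by letter: "Patients will be randomly allocated to the intervention group (A) and the control group (B) in a ratio of 1:1". It then gives the contents. Group A receives the nitrous oxide/oxygen mixture, and "group B will receive oxygen plus conventional treatment (no analgesic) under the same conditions".

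The same paragraph says who is blind: "Doctors, therapists, patients, and data collectors are all blind to the study". It also describes how the allocation travels: "Nurses who implemented the intervention handed the doctors envelopes containing the patients’ codes and allocation of A or B".

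The section Randomization, allocation, concealment and blinding gives another account. The project manager requests the random number once eligibility and baseline assessment are complete. On knowledge of the assignment it says: "Except for the project manager, who is responsible for gas distribution, other researchers, operators, and patients do not know the allocation". The masking device is that the look-alike cylinders of both gases "will be covered with labels A and B until completing all the procedures of this trial". The section also allows code breaks for individual patients in exceptional circumstances.

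The Intervention section adds that nurses administer the gases.

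**The concern.** A double blind that works through a label depends on the label carrying no information about treatment. Here the label is one of two letters used for every patient, and the article prints those letters beside the treatments. The doctors, who are listed as blind, are also described as receiving the A/B allocation, although the methods section confines knowledge of it to the project manager.

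This matters because the main endpoints depend on perception. The primary outcome is pain on a patient-completed VAS, and the Limitation section accepts that it is open to subjective influence. Satisfaction of patient and therapist, use of adjuvant analgesia and willingness to have the same gas again are open to expectation too. The article states a hypothesis in favour of nitrous oxide. If those treating, assessing or analysing know the arm, any resulting bias would plausibly run in that direction.

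**Working it through.** No sample size, power or alpha figure bears on this point. The check compares the statements and then counts patients.

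**Step 1. Who knows the allocation.**
- Abstract: doctors, therapists, patients and data collectors are blind.
- Abstract: nurses hand doctors envelopes holding the patient code and the A/B allocation.
- Methods: only the project manager, who distributes the gas, knows the allocation.

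The second statement conflicts with the third unless the letter is meaningless to those who hold it. It also describes a different route, nurse to doctor rather than through the project manager.

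**Step 2. Whether the letter is meaningless.** There are two possible readings.
- *Cylinder letter equals group letter.* This is the natural reading, because no other key is given. The key is then in the article itself, and anyone who knows it and sees a cylinder or an opened envelope knows the gas. Identical cylinders do not help.
- *Cylinder letters are scrambled against group letters.* The article's key then does not decode a cylinder. Two labels still serve the whole trial, so decoding one decodes the other.

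**Step 3. Reach of one disclosure under two labels.** Inputs: N = 120 and 1:1 allocation (Study design).
- Patients per letter: 120 / 2 = 60.
- Learning the gas behind one letter reveals 60 patients directly and 120 − 60 = 60 by elimination, so 120 in all, to anyone who also knows the patients' letters.
- With one code per patient, one code break reveals 1 of 120. With one code per cylinder, it reveals only the patients who used that cylinder.

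**Step 4. How much of that reach can affect outcomes.** VAS and satisfaction are recorded by T2, 5 min after the intervention finishes. A disclosure after k patients have been assessed cannot alter those k sets of scores, so it can influence at most 120 − k patients.
- k = 0: 120 patients.
- k = 98 (the number included at the time of writing, Trial status, taking their assessments as complete): 120 − 98 = 22 patients, which is 22 / 120 = 18%.

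Blinding of data handling and analysis is different: it can be lost for all 120 at any time before the database is closed and analysed.

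**Step 5. Side effects as a second route.** The article lists dizziness, euphoria and lethargy among the effects. One such patient raises a suspicion about one letter. Over repeated patients and daily sessions, staff can link a letter to a pattern and carry that knowledge to the next patient with the same letter. Unique codes cannot hide an effect within one patient, but they stop the carry-over.

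**The case against.** The strongest reply is that this is a condensed article, and that label coding, envelope handling and the emergency unblinding system are details left to the full protocol. The group letters appear only in the abstract. The methods section uses A and B only for cylinders, and nowhere says that cylinder A holds group A's gas. The envelopes may be sealed, and not knowing the allocation may mean not knowing the gas. Doctors are not named as outcome assessors. Patients score their own pain and need not see the letter or know its meaning.

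Much of this stands, and it rules out several stronger readings that a reader might infer:
- *That every party is unblinded.* The documents do not show it, and the direction of any bias is plausible rather than demonstrated.
- *That allocation concealment is broken.* The methods section keeps the list sealed with an administrator outside the study, and a number is requested only after baseline. A letter on a cylinder does not reveal the next assignment.
- *That one euphoric patient decodes the scheme.* That gives a suspicion, not a key.
- *That 120 of 120 measures bias.* It measures the reach of a disclosure. Scores already recorded are not affected.

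The reply does not remove the point, which rests on what the article states rather than on what it leaves out: a two-letter mask, the same two letters published as arm names, and two accounts of who holds the allocation that do not agree.

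**Conclusion.** The masking, as described, does not secure the stated double blind. On the natural reading the cylinder carries the arm name. On the more favourable reading, one code break, or an accumulated pattern of side effects, would reveal the gas for every patient sharing the letter and, by elimination, for the rest. The practical exposure at the time of writing is the 22 of 120 patients still to be enrolled, together with data handling and analysis for all 120. For the 98 already included, the open question is who had seen the letters and knew their meaning, which the article does not answer.

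This rests on two assumptions: that the two letters are the only code in use, since no other is described, and that the 98 had completed their assessments. If some had not, more than 22 remain exposed.

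**What to change.** 1. For the remaining patients, replace A and B on cylinders, envelopes and forms with unique cylinder- or patient-level codes unrelated to the arm names. Only the uninvolved administrator and the project manager should hold the key, and an emergency code break should open one code only.
2. Use a separately scrambled arm code in the analysis dataset.
3. Reconcile the abstract with the methods section on who receives and who can read the allocation, and state whether cylinder letters match group letters.
4. For patients already treated, report who had access to the A/B code and who knew its meaning. This still applies if recruitment has closed.

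A sensitivity analysis by labelling period is not worth adding. With 22 patients after the change, about 11 per arm, it would not be informative.

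The cost is relabelling, recoding the rest of the list and a short amendment. Under the article's Ethics and dissemination section, the amendment needs agreement within the trial team, ethics approval before use, and notification. If that arrives too late to help enrolment, items 2 to 4 can still be done. The sample size does not change.

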### Intervention

After inclusion in the study, participants will be randomized into intervention and control groups. All procedures will be carried out in the rehabilitation treatment hall. MT includes passive joint movement and joint stretching for a total of 30 min. The procedure is performed by qualified rehabilitation therapists who have worked for more than 2 years in the hospital. And the two gases implemented are conducted by trained and qualified nurses. Before and after the MT, wax therapy, and cold compress are applied as routine treatments. The patients in the intervention group began inhaling pre-mixed 65% N_2_O through a specially designed mask with a check valve, 2 min before MT, and continue the whole procedure until it ends, while the control group inhaled 100% oxygen under the same conditions. The gas will be administered by the patients themselves in order to observe their state of consciousness. Blood pressure will be measured before, during, and after each MT, and the oxygen saturation and heart rate were continuously monitored with a pulse oximeter throughout the process. Image and audio recordings will be taken individually for communication coding and data analysis. Adjuvant analgesics will also be recorded.

